#### Randomization

Patients are informed about both treatment approaches and are willing to participate in a random assignment. Randomization is conducted in two patient pairs with a 50–50% assignment to one of the two therapeutic modalities using the program BiAS 11.02 [61]. Randomization is stratified by gender to control for the gender distribution in each treatment modality.

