In sum, there are promising findings on the clinical efficacy and effectiveness of DBT and ST in treating BPD [20]. Moreover, both treatments lead to impressive reductions in direct and indirect health care costs (approx. 10,000 € per patient per year) [30, 51]. However, research has not yet compared these two methods. A treatment comparison would be interesting for psychotherapy research because both treatments have different approaches to treating BPD and focus on different techniques, despite several common factors (see also methods and a detailed overview in [55]).

The objective of this study is to compare the (cost)-effectiveness of DBT and ST in patients who have BPD. The PRO*BPD trial is the first randomized trial to compare these two methods. The primary hypothesis is that DBT and ST significantly differ in reducing BPD-severity (two-sided hypothesis). A two-sided hypothesis was chosen because information from literature does not allow predictions on the directionality of the difference (see discussion for more information on this theme).

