#### Sample size

The primary variable for calculating the sample size is the BPDSI total score. The sample size calculation is based on the number of participants that are needed to detect a clinically significant difference between the two conditions. Although the meta-analyses on DBT demonstrated global changes in effect sizes (ES) of d = 0.5 [27] and ST had a higher change in ES for borderline-specific symptoms (d = 2,96 [45] and d = 2.81 [44]), these cannot reliably be compared because they reflect different samples and outcome instruments, and there has been no direct comparison between the two methods. Therefore, we chose a medium ES of d = 0.5 for detecting group differences for the sample size calculation. Detecting a difference with this ES could strongly influence clinical decision making. As such, *n* = 64 patients per condition are required to detect group differences with a Type I error of 5% and a power of 80% (Type II error = 20%). Assuming an attrition rate of 20%, we will recruit *n* = 160 patients.

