### Treatments

#### Common framework

The structural conditions of both treatment programs are as similar as possible to guarantee clinical equipoise: In both groups, patients receive a combined program of one group therapy session (120 min) and one individual therapy session (60 min) per week for a maximum of 18 months. Patients receive 4–10 weekly individual sessions before beginning the 18 months combined program to become accustomed to their individual therapist and the treatment model, as well as to be prepared for the group sessions. The exact number of individual sessions, which a patient receives, preceding the combined treatment program, is determined by the availability of treatment slots of the individual therapist. With absences that are due to illness, holidays or other disruptions, we estimate that each patient has an average therapy dose of 65 individual sessions and 60 group sessions. The groups consist of a maximum of ten patients and are conducted by two therapists. Groups are offered in a semi-open format. Thus, when treatment slots for patients are available (e.g., because of treatment drop-out or early success of a patient), new patients will enter the group. Thus, this format compensates for dropout and allows new study patients to begin more quickly than in a closed group. The time spots where new patients enter the group will be planned between research and therapist team and are dependent on a variety of points: available treatment slots in the group treatment and a time point that is suitable from a therapeutic stance to include new patients (e.g. after ‘group holiday’ or termination of a specific therapeutic theme), availability of an individual therapist to offer weekly individual sessions with at least four sessions preceding entry of the patient in the group treatment and completeness of baseline assessments. Eligible patients who are not able to attend group sessions due to family, professional or educational duties are included in the trial and are provided individual therapy only. In both conditions, patients can call their individual therapists outside of the sessions for support (a major component in DBT and to a lesser degree in ST). However, telephone support by the individual therapist is limited to office hours (which is normally not the case in DBT) to respect the participating therapists’ personal boundaries and to provide the same conditions for each patient. Outside of office hours, the psychiatric emergency service of our department is available for patients at any time. All patients also receive psychiatric management in our center. Additional medication is prescribed as needed according to national guidelines. According to our experience with BPD patients, this will reduce pre-existing polypharmacotherapy. Medication will be statistically controlled for in the data analyses.

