#### Statistical analyses of the clinical effectiveness study

Data analyses will be performed based on the intention-to-treat principle (including all patients regardless of whether they drop out from treatment or not) and will use all available data. Data for the primary and most secondary outcome measures will be analyzed with multilevel analysis to compare DBT to ST (mixed regression models for repeated measures). Time will be modelled according to the best model fit, e.g., a linear, logarithmic, or a segmented development of scores over time. The treatment by time interaction will be the primary test for treatment differences. We will use a piece-wise regression model if preliminary inspection of the data indicate that the time development during treatment has a different slope than during the follow-up period. If the time-development is better represented by a continuous equation (e.g., time, or SQRT (time), or log (time)) than we will do sensitivity tests of the treatment x time interaction for the treatment period, in addition to the test for the whole assessment period. We will also examine the between group differences at specific time-points, e.g., at the end of treatment and the final follow-up. For categorical outcome variables, counts appropriate forms of mixed regression will be chosen, with attention to non-normal residuals (negative binomial, Poisson, and gamma, etc.). Mixed regression methods will also be used to identify predictors/moderators that are related to treatment outcomes. Survival analysis will be used to analyze treatment retention.

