Another limitation is that in some areas we had to deviate from the standard treatment manuals to guarantee clinical equipoise, to optimally deal with our severely ill patients or to adapt to the possibilities and limitations of the outpatient center of Lubeck University. There are some essential deviations from standard DBT that should be named: To protect the boundaries of the participating therapist we decided not to provide 24-h-telephone counselling, and we decided on another definition for treatment termination as explained in the methods section.

As another strength of the study treatment integrity will be checked However, the psychometric evaluations of the adherence scales are not published, which is a major limitation.

There are several other limitations due to the ‘real world’ character of the study. Because we rely on free treatment slots for individual and group treatments there will be variability in the range of 4–10 individual sessions patients will receive preceding the combined treatment program of group and individual and also the average of total individual and group sessions will vary. Some patients, who are not able to attend the group sessions, will also be part of the analyses. These patients will be equally randomized between ST and DBT-oriented treatment (DBT without group treatment is not standard-DBT). However, this is of course a limitation.

In conclusion, the PRO*BPD trial will significantly extend our knowledge on psychotherapy for BPD. Both DBT and ST hold promise for treating BPD. By examining the two methods’ clinical effectiveness over a broad spectrum of outcome parameters while performing an economic evaluation and assessing major stakeholder’s experiences, this study will significantly contribute to developing best practices for treating BPD and associated problems.

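### The primary treatment-by-time test, as described, neither holds the arms equal at baseline nor names the stratification factor; it is valid but may waste precision

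*Protocol article*

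**What the plan says.** All references are to the protocol article.

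- **Randomization:** assignment is 50–50 in pairs. On stratification: "Randomization is stratified by gender to control for the gender distribution in each treatment modality". No other factor is named.
- **Statistical analyses of the clinical effectiveness study:** a mixed regression model for repeated measures, by intention to treat, on all available data. Time takes whatever form fits best. "The treatment by time interaction will be the primary test for treatment differences". The section lists no covariates.
- **Assessment and outcome measures:** BPDSI is measured at baseline, with one assessment directly before randomisation, then at 6, 12 and 18 months and three times in follow-up.
- **Sample size:** "Therefore, we chose a medium ES of d = 0.5 for detecting group differences for the sample size calculation". The section asks for 64 per condition at 5% Type I error and 80% power, and recruits 160 to allow for 20% attrition.
- **Common framework:** "Eligible patients who are not able to attend group sessions due to family, professional or educational duties are included in the trial", with individual therapy only. The Discussion says of them: "These patients will be equally randomized between ST and DBT-oriented treatment".

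**The concern.** Randomisation makes the expected baseline BPDSI the same in both arms. A treatment-by-time model that still estimates a separate baseline difference does not use that fact. It measures each patient's change from a noisy starting value, so the interaction has roughly the precision of a change score. Holding the arms equal at time zero, or adjusting for baseline, recovers what is lost.

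The article fixes the interaction as the primary test but does not say which version is meant. This matters because the trial compares two active therapies, and the Discussion accepts that an effect smaller than medium might be missed.

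There are two smaller points. A factor used to stratify allocation is normally carried into the analysis, and gender is not named there. And the Discussion's wording about patients who cannot attend the group could be taken as a promise of equal numbers, which stratification by gender alone does not secure.

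**Working it through.** **1. The plan's own figure.** Inputs from Sample size and Background: d = 0.5 (so SD = 1), two-sided 5%, power 80%, attrition 20%. The exact two-sample t-test gives 63.8, so 64 per arm, with power 0.801. Then 128 / (1 − 0.20) = 160. Both figures reproduce, and neither relies on baseline adjustment. With the normal approximation used below, 64 per arm gives 0.807 for an unadjusted end-point comparison.

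**2. The interaction test with and without a common baseline mean.** Assumptions:
- visits at 0, 6, 12 and 18 months, scaled to t = 0, 1/3, 2/3, 1;
- SD 1 at every visit and the same correlation ρ between any two visits;
- a treatment difference growing linearly to 0.5 SD at 18 months;
- n = 64 per arm, complete data.

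The article gives no ρ, so a range is shown.

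- Free baseline difference: Var = 2(1 − ρ) / (n·S), where S = Σ(t − mean t)² = 0.5556, so n·S = 35.56.
- Common baseline mean: Var = 2 / (n·C), where C = [Σt² − ρ(Σt)²/(1 + 3ρ)] / (1 − ρ), Σt² = 1.5556 and Σt = 2.
- Power = Φ(0.5/SE − 1.96).

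| ρ | SE, free | Power, free | C | SE, common | Power, common |
|---|---|---|---|---|---|
| 0.3 | 0.198 | 71% | 1.320 | 0.154 | 90% |
| 0.4 | 0.184 | 78% | 1.380 | 0.150 | 91% |
| 0.5 | 0.168 | 85% | 1.511 | 0.144 | 94% |
| 0.6 | 0.150 | 92% | 1.746 | 0.134 | 96% |
| 0.7 | 0.130 | 97% | 2.174 | 0.120 | 99% |

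The free version reaches 80% when 2(1 − ρ)/35.56 = 0.25/(1.96 + 0.8416)² = 0.03185, that is at ρ ≈ 0.43.

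**3. Cross-check with one follow-up visit.** The variance factor is 2(1 − ρ) for a change score and 1 − ρ² with baseline adjustment. At ρ = 0.4, 0.5 and 0.6, power is 73%, 81% and 89% against 87%, 90% and 94%. The pattern is the same.

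**4. Gender.** Assume 20% men and a gender difference of 0.2 to 0.5 SD. For an end-point comparison, omitting gender overstates the SE by √(1 + 0.2·0.8·g²): 1.003 at g = 0.2 and 1.020 at g = 0.5, so 0.3% to 2%. If gender explains 1%, 5% or 10% of the variance, the actual Type I error is 2[1 − Φ(1.96/√(1 − R²))] = 0.049, 0.044 or 0.039. Under compound symmetry, a gender effect that is constant over time falls out of the free-baseline interaction, so these figures are at the high end for that test.

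**5. Patients who cannot attend the group.** Their number is not given. Assume 8, 16 or 24 of 160, with 80 per arm. By the hypergeometric distribution, the chance of an exactly equal split is 28%, 21% or 17%. With 16 such patients, a 12/4 or worse split has a 6% chance. If they differ prognostically by 0.3 to 0.5 SD, a 12/4 split moves the treatment contrast by 0.3 × 8/80 = 0.03 to 0.5 × 8/80 = 0.05 SD.

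**The case against.** The strongest reply is that this is a journal article and covariate lists usually sit in the analysis plan, which is not at hand. The statistics section is plainly not a full list of model terms, because Common framework separately says that medication will be controlled for. Whether the arms are constrained at time zero is a parameterisation choice, and both versions are accepted. The power comparison rests on assumed correlations and on linear time, while the plan lets the data choose the time form. At ρ = 0.5 or above even the free version exceeds 80%.

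Most of this stands, and it limits the point. Several stronger readings are tempting and are not supported:

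- **That baseline BPDSI and gender are unused.** Baseline is naturally the time-zero response, so it is used. Gender is not stated as a term, which is not the same as being excluded.
- **That the test is invalid or the sample size wrong.** Neither follows. Omitting gender errs on the conservative side.
- **That the Discussion contradicts the Randomization section.** Read as the same 50–50 chance for each patient, the two agree. Only a reading as equal numbers is unsecured.
- **That uneven numbers of individual-only patients would confound the comparison.** Chance imbalance under randomisation is part of the sampling error that the test already allows for. The Discussion also declares the inclusion of these patients a limitation.

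What the objection does not remove is that the article commits to the interaction as the primary test and leaves unsaid the one feature that decides how precise it is.

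**Conclusion.** The point holds as one of precision and clarity. The size of the loss depends on a correlation that the article does not give. It is about 19 percentage points of power at ρ = 0.3 (90% − 71%), 9 at 0.5 (94% − 85%) and 2 at 0.7 (99% − 97%). Below about 0.43 the unconstrained form misses the planned 80%. These figures rest on four visits, linear growth of the effect, equal SDs, compound symmetry and 64 complete patients per arm. Another time form, random slopes or use of the follow-up visits would change them, but the common-baseline version would still be at least as precise. Adding gender is good practice with a small gain. The sentence about patients who cannot attend the group is a matter of wording.

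**What to change.** 1. State that the primary mixed model constrains the two arms to a common mean at the pre-randomisation BPDSI, so that the treatment-by-time terms carry the whole treatment effect. Alternatively, use baseline BPDSI as a covariate with post-baseline visits as outcomes. In that case the primary contrast must be a treatment difference at a named visit or over named visits. An interaction among post-baseline visits alone would miss any difference already present at 6 months.
2. Include gender as a prespecified fixed effect.
3. Optionally, where ability to attend the group was recorded before randomisation, add it as a covariate.
4. Reword the Discussion to say that patients who cannot attend the group have the same 50–50 chance of either arm, without implying equal numbers.

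Do not add a randomisation stratum. It would change the allocation scheme of a trial already registered and, with allocation in pairs, leave more incomplete pairs. The cost of the rest is a few sentences and a small amount of analysis work. The sample size does not change.

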### Treatments

#### Common framework

The structural conditions of both treatment programs are as similar as possible to guarantee clinical equipoise: In both groups, patients receive a combined program of one group therapy session (120 min) and one individual therapy session (60 min) per week for a maximum of 18 months. Patients receive 4–10 weekly individual sessions before beginning the 18 months combined program to become accustomed to their individual therapist and the treatment model, as well as to be prepared for the group sessions. The exact number of individual sessions, which a patient receives, preceding the combined treatment program, is determined by the availability of treatment slots of the individual therapist. With absences that are due to illness, holidays or other disruptions, we estimate that each patient has an average therapy dose of 65 individual sessions and 60 group sessions. The groups consist of a maximum of ten patients and are conducted by two therapists. Groups are offered in a semi-open format. Thus, when treatment slots for patients are available (e.g., because of treatment drop-out or early success of a patient), new patients will enter the group. Thus, this format compensates for dropout and allows new study patients to begin more quickly than in a closed group. The time spots where new patients enter the group will be planned between research and therapist team and are dependent on a variety of points: available treatment slots in the group treatment and a time point that is suitable from a therapeutic stance to include new patients (e.g. after ‘group holiday’ or termination of a specific therapeutic theme), availability of an individual therapist to offer weekly individual sessions with at least four sessions preceding entry of the patient in the group treatment and completeness of baseline assessments. Eligible patients who are not able to attend group sessions due to family, professional or educational duties are included in the trial and are provided individual therapy only. In both conditions, patients can call their individual therapists outside of the sessions for support (a major component in DBT and to a lesser degree in ST). However, telephone support by the individual therapist is limited to office hours (which is normally not the case in DBT) to respect the participating therapists’ personal boundaries and to provide the same conditions for each patient. Outside of office hours, the psychiatric emergency service of our department is available for patients at any time. All patients also receive psychiatric management in our center. Additional medication is prescribed as needed according to national guidelines. According to our experience with BPD patients, this will reduce pre-existing polypharmacotherapy. Medication will be statistically controlled for in the data analyses.

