### Cost-effectiveness study

#### Assessing resource consumption and productivity loss

Costs are assessed from several societal perspectives, including direct medical, direct non-medical and indirect costs, through structured face-to-face interviews (“Cost Interview”). The Cost Interview was used in another German study [10, 30] that examined the cost of BPD. Prior to the current study, modifications were made to improve clearness/comprehensibility, and additional items were incorporated into the Cost Interview. Items that are related to direct resource consumption include psychiatric and general hospital days, days in a psychiatric day clinic and assisted living programs, drug intake, visits to emergency rooms, outpatient psychotherapists, psychiatrists, general practitioners, medical specialists, occupational therapists, physical therapists, community based counselors and crisis centers. Items that are related to non-medical resource consumption include informal care, which occurs when significant others take over domestic tasks without payment. Also, we assess incidents of deviant behavior (e.g., traffic offenses, bodily harm) and their associated consequences, such as police operations or monetary compensation for damages. Productivity loss is captured with questions on employment status, the source of income, gross income, the number of weeks of employment, unemployment and work disability since the last assessment. Employed patients are asked about their average weekly work hours and the number of days that they were absent from work.

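### The plan to control for medication is not limited to baseline; on its nearest reading it adjusts the DBT–ST comparison for as-needed medication taken after randomisation

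*Protocol article*

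**What the plan says.** The passage is the end of the Common framework section of the protocol article. Four consecutive sentences matter:

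- The first gives psychiatric care at the study centre to every participant, so it applies to both arms.
- The second deals with prescribing while the trial runs: "Additional medication is prescribed as needed according to national guidelines".
- The third gives the authors' expectation of what follows from these arrangements: "According to our experience with BPD patients, this will reduce pre-existing polypharmacotherapy".
- The fourth is the sentence at issue here, on the analysis: "Medication will be statistically controlled for in the data analyses".

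The section on statistical analyses of the clinical effectiveness study sets the analysis principle ("Data analyses will be performed based on the intention-to-treat principle") and the primary test: "The treatment by time interaction will be the primary test for treatment differences". It does not mention medication.

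Medication is recorded repeatedly. The Cost Interview includes "drug intake, visits to emergency rooms, outpatient psychotherapists" among its items, and Table 2 schedules that interview at baseline and at every later assessment. A medication covariate that changes over time is therefore feasible.

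**The concern.** Baseline medication is fixed before allocation and can be adjusted for safely. Medication taken during the 18 months is different: it is prescribed in response to how the patient is doing. The primary hypothesis is that the two therapies differ in reducing BPD severity. If they do, symptom-driven prescribing will tend to differ by arm, and medication becomes partly a consequence of allocation.

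Conditioning on such a variable does two things. It removes any part of the treatment effect that runs through medication. It also links allocation to unmeasured prognosis, because patients with the same medication in the two arms are no longer comparable in the symptoms that led to it. The estimate is then not the total DBT–ST effect that an intention-to-treat comparison is meant to deliver. A real difference could be understated or overstated, and a small one could appear where none exists if the arms differ only in prescribing.

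**Working it through.** **1. The plan's own figure.** The sample size rests on d = 0.5, two-sided 5% error and 80% power.
- The normal approximation gives 63 per arm. The two-sample t-test gives 63.77, so 64 per arm, as stated.
- 128 / (1 − 0.20) = 160, as stated.
- Power at 64 per arm is 0.801 (t-test).

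The calculation is for an unadjusted comparison of two groups. The point here concerns what is estimated, so these figures do not change.

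**2. Which medication is meant?** Two readings are possible.
- Baseline medication: the preceding sentence mentions medication that patients already take.
- Medication during the trial: the sentences before it describe prescribing in the trial and change from the starting level, and the sentence carries no limit to baseline.

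The second is the nearer reading. Nothing elsewhere in the article confines the adjustment to baseline or to a sensitivity analysis.

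**3. Size in a simple linear model.** All inputs are assumed; the documents give none. Outcome, and medication within arm, are in SD units. The better arm lowers medication by a = 0.3. An unmeasured prognostic factor loads 0.4 on both medication and BPDSI. The medication–BPDSI slope is b, where a positive b means that more medication goes with worse symptoms and a negative b means that medication helps. The true total effect is 0.50.

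Adjusted effect = 0.50 − a × (b + 0.4²) = 0.50 − 0.3 × (b + 0.16)

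| b | Calculation | Adjusted effect |
|---|---|---|
| +0.3 | 0.50 − 0.3 × 0.46 | 0.36 |
| 0 | 0.50 − 0.3 × 0.16 | 0.45 |
| −0.16 | 0.50 − 0.3 × 0 | 0.50 |
| −0.2 | 0.50 + 0.3 × 0.04 | 0.51 |
| −0.3 | 0.50 + 0.3 × 0.14 | 0.54 |

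If the better arm instead raised medication by 0.3 SD, the signs flip. For b = +0.3 the result is 0.50 + 0.138 = 0.64; for b = −0.3 it is 0.50 − 0.042 = 0.46.

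**4. A second model with symptom-driven prescribing.** Medication here responds to mid-treatment symptoms with coefficient c, and directly to arm by a stated shift. Baseline severity is in every model, there are 64 patients per arm, and all parameters are again assumed. In these rows medication has no effect of its own on symptoms.

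| Scenario | Effect adjusted for baseline medication | Effect adjusted for on-treatment medication | Power, baseline → on-treatment |
|---|---|---|---|
| Medication unrelated to arm and symptoms | 0.50 | 0.50 | 0.85 → 0.85 |
| c = 0.3, no direct arm shift | 0.50 | 0.47 | 0.85 → 0.82 |
| c = 0.5, no direct arm shift | 0.50 | 0.43 | 0.84 → 0.75 |
| c = 0.3, better arm 0.3 SD lower | 0.50 | 0.41 | 0.83 → 0.67 |
| c = 0.3, better arm 0.3 SD higher | 0.50 | 0.53 | 0.84 → 0.89 |
| No symptom effect, arms differ by 0.3 SD in prescribing, c = 0.3 | 0.00 | about 0.06, either direction | not computed |
| No symptom effect, no prescribing difference, c = 0.3 | 0.00 | 0.00 | not computed |

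When medication was also allowed to lower symptoms (slope −0.2), the two distortions happened to cancel: adjusted and unadjusted effects were both 0.42 with the better arm lower on medication, and both 0.55 with it higher. Baseline-medication adjustment matched the unadjusted effect in every scenario.

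Both models are regressions at a single time point. The shift in the planned treatment-by-time interaction of a mixed model was not examined.

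**The case against.** The strongest defence is that the sentence decides nothing. It sits in the treatment description, names no variable or model, and the statistical section gives the primary test without any medication term. Covariate lists are commonly left to an analysis plan, which is not shown here. Baseline medication may be what was meant, and then there is no problem. This stands in part: the point is conditional, and it is not established that the primary model will contain on-treatment medication. It does not dispose of the point, because the article makes a positive commitment rather than omitting a detail, and nothing in it limits that commitment to the harmless version.

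Three stronger readings are tempting and are not supported.

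- A reader might infer that the authors expect DBT or ST to reduce medication. The expected fall is attributed to psychiatric management and guideline prescribing, which both arms receive. No difference between arms is predicted.
- A reader might call the sentence a contradiction of intention to treat. The statistical section explains that principle by who is analysed, namely all patients whether or not they drop out. A covariate excludes nobody. The tension is over what is estimated.
- A reader might infer a markedly inflated false-positive rate from the simple model with b = +0.3, where a zero total effect would appear as 0.3 × 0.46 = 0.14. Of that, 0.3 × 0.3 = 0.09 is a direct effect built into the assumptions, so it is not a measure of spurious findings. A range that admitted only positive slopes would also wrongly suggest that the bias always runs towards a smaller effect.

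**Conclusion.** The point holds in conditional form and should be fixed. As written, the sentence permits, and on its nearest reading plans, adjustment for a variable measured after randomisation that responds to symptoms. If the arms differ in symptoms or prescribing, that adjusted comparison does not in general estimate the total randomised effect.

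Neither size nor direction can be derived from the documents. With a 0.3 SD lower medication level in the better arm, a shared prognostic loading of 0.4 and slopes from +0.3 to −0.3, a true 0.50 SD effect is estimated as roughly 0.36 to 0.54. With symptom-driven prescribing the figures were 0.41 to 0.53. The distortion is zero if medication is unrelated to arm and symptoms, and it can cancel by chance. Because it cannot be predicted, the rule should be settled before analysis.

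**What to change.** Replace the sentence under Common framework with:

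> The primary treatment by time test and other treatment comparisons are not adjusted for medication taken after randomisation; only baseline medication may enter as a covariate. Medication during treatment is reported by arm, and any analysis adjusting for it is labelled exploratory (e.g. mediation).

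The Background already provides for exploratory work on mediating variables, so such an analysis has a place. The cost is one sentence. No new data or patients are needed, since drug intake is already collected at each assessment, and the sample size of 64 per arm and 160 in total is unaffected.
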